9.1.7 Reporting of SAEs to Health authorities and IEC/IRBs

Medicago R&D Inc. will be responsible for reporting SAEs that are deemed possibly related to test article and unexpected (Unexpected refers to not appearing in the package labelling or in the study vaccine Investigator’s Brochure to regulatory authorities in an expedited manner.

The Investigator will be responsible for reporting all SAEs directly to their relevant ethical review body (IEC/IRB) as soon as possible, and will also provide the ethical review body with any safety reports prepared by the study Sponsor.

9.1.8 Seven (7) - Day Safety Monitoring

A review of 7-day safety data will be carried out to ensure ongoing safety of study subjects as well as maintaining study scientific integrity. This review will detect any early negative trends in the safety data and may necessitate a decision to return to a lower dose level. A telephone call reminding study subjects to complete the Memory Aid will be made at Day 1 post-vaccination. Eight (8) days following each vaccination, subjects will be telephoned by clinic staff to review and record 7-day safety data. Early accumulated safety outcome data which will include all self-reported solicited local and systemic symptoms, any adverse and / or serious adverse events occurring following administration of each injection at the first two dose levels, will be collected and tabulated.

The safety experts will be provided the following blinded 7-day solicited local and systemic symptoms:

- Occurrences of erthyema, swelling and pain at the injection site
- Occurrences of fever, headache, muscle aches, joint aches, fatigue, chills, and feelings of general discomfort or uneasiness
- Swelling in the axilla, groin, neck or chest
- Occurrence of any adverse or serious adverse events
- Oral temperature results from the first seven days post vaccination will also be provided
- Concomitant medications, doctor or emergency room or hospital visits associated with an adverse event or serious adverse event

Safety data for all subjects in the first cohort receiving the 5µg dose or placebo, will be tabulated and reviewed by the Investigator and 2 medical advisors, prior to permitting the second cohort to receive a higher dose (10µg) or placebo, of study vaccine. The same procedure will be repeated with the second cohort of sixteen subjects. Following a favourable review of the second cohort, who received 10µg of study vaccine or placebo, this cohort’s seven-day safety data, will be reviewed. Following a favourable review, cohort 3 subjects will be permitted to be randomized to the highest dose level (20µg). There will be one safety review following the first dose of the 20µg dose level. In total, there will be five (5) seven-day safety reviews following each injection from cohort 1 and cohort 2. Due to the timeframe of the analysis involved, the seven – Day safety data may not be monitored for the purposes of the 7-day safety report, but these data will be monitored in advance of the interim study report.

This safety data may be un-blinded based on the reviewers’ medical judgement.

Stopping rules or conditions for stopping this clinical trial would occur if there was clear evidence of harm or harmful side effects such as Serious Adverse Events related to the treatment (study vaccine). A Serious Adverse Event which was thought to be unrelated to the study vaccine would not warrant stopping the trial.

Based on the medical experts’ opinion, the following criteria may result in the stopping of the clinical trial:

- - - More than one (1) SAE probably related to the study vaccine.
    - Solicited Local injection site symptom reactions >grade 2 (moderate) severity = > 70%
    - Solicited Systemic symptom reactions > grade 2 (moderate) = > 50%

Refer to a sample outline of the safety narrative in Appendix C.

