The safety experts will be provided the following blinded solicited local and systemic symptoms tabulated for the first 7 days post-vaccination: erythema (redness), swelling and pain at the injection site. The following blinded systemic symptoms will be provided for review: occurrence of headache, fever, myalgia (muscle aches), arthralgia (joint aches), fatigue, chills, and feelings of general discomfort or uneasiness, swelling in the axilla, groin, neck or chest, as well as the occurrence of any adverse or serious adverse events. Oral temperature results from the first seven days post vaccination will also be provided. These data may be un-blinded based on the reviewer’s medical judgement. Refer to Section 9.1.8 for further information.

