5.1.2 Trial Design and Plan

Subjects will be enrolled in the study in a staggered fashion. Refer to Figure 2 below. Study enrolment will begin with two (2) subjects from Cohort 1 on Day 0; one subject will be randomized to receive the 5µg dose of plant-based H5 VLP (H5N1) pandemic influenza vaccine combined with Alhydrogel® intramuscularly and one subject will be randomized to receive the placebo preparation, 100mM phosphate buffer + 150mM NaCl + 0.01% Tween 80 combined with Alhydrogel®. Subsequently, the following day, 3 subjects will be randomized to receive H5 VLP (H5N1) pandemic influenza vaccine and 1 subject will be randomized to receive the placebo preparation. On Day 2 of the study, 4 subjects will be randomized to receive H5 VLP (H5N1) pandemic influenza vaccine and 1 subject will be randomized to receive the placebo preparation. On Day 3 of the study, 4 subjects will be randomized to receive H5 VLP (H5N1) pandemic influenza vaccine and 1 subject will be randomized to receive the placebo preparation, for a total Cohort of 16 subjects. Once all Cohort 1 subjects have completed Day 7, a blinded safety report will be generated and reviewed by a panel consisting of the Investigator and two independent, expert medical advisors. A favourable 7-day safety report will permit the initiation of the vaccination of Cohort 2 at the 10µg dose level. A second blinded safety report will be conducted following the second vaccination at the 5µg dose level. A blinded seven-day safety report evaluating the safety of subjects receiving the 10µg dose will be generated in the same manner, in addition to a safety report being generated seven days following the second 10µg dose of study vaccine. Study vaccine dose escalation to 20µg will only be permitted if safety data is favourable, as judged by the Investigator and medical safety experts. Safety reports will be generated following the first and second dose of vaccine at the 5 µg and 10µg dose levels, and after the first dose of the 20µg dose level is completed, for a total of 5 reports.

The proposed randomization schedule is described below.

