6.7 Blinding and Code Breaking Procedures

The randomization code will not be broken except in emergency cases wherein the identification of the treatment is necessary for appropriate treatment of the subject. A sealed envelope containing the un-blinded randomization schedule may be kept in a locked, secured location at the clinical site. In such circumstances, the un-blinded randomization code may be opened with the permission of the Sponsor Medical Monitor and the treatment assignment would be revealed.

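### The advisory 70% and 50% limits for reactions above grade 2 name no denominator; read from the default blinded 16-subject report, they do not measure the vaccine arm

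*Protocol*

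**What the plan says.** Section 9.1.8 states that, on the experts' opinion, "the following criteria may result in the stopping of the clinical trial". Besides a criterion on related serious adverse events, it lists two percentages:

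- local: "Solicited Local injection site symptom reactions >grade 2 (moderate) severity = > 70" (per cent);
- systemic: "Solicited Systemic symptom reactions > grade 2 (moderate) = > 50" (per cent).

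Appendix C repeats both and adds only that they apply at any dose.

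On what the panel sees, section 5.1.2 says that "a blinded safety report will be generated and reviewed by a panel consisting of the Investigator and two independent, expert medical advisors", and section 9.1.8 says that "The safety experts will be provided the following blinded 7-day solicited local and systemic symptoms". Section 9.1.8 also has the data of all cohort subjects, on vaccine or placebo, tabulated for the review. Section 5.1.1 sets each cohort at 16 subjects, 12 on vaccine and 4 on placebo. The sample tables in Appendix C list reactions by symptom and day, without a treatment-arm column.

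On un-blinding, section 9.1.8 allows it at the reviewers' medical judgement ("This safety data may be un-blinded based on the" reviewers' judgement), and section 5.1.1 says the same ("These data may be un-blinded based on the" reviewer's judgement). Section 6.7 says "The randomization code will not be broken except in emergency cases" and does not mention this route.

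On the number of reviews, section 5.1.1 gives four. Sections 5.1.2 and 9.1.8 give five.

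**The concern.** A percentage limit needs a numerator, a denominator and an inequality sign, and the protocol fixes none of these fully. It does not say whether the base is vaccine recipients or the whole cohort, whether subjects or reactions are counted, or whether any symptom or each symptom counts. The sign is printed as an equals sign followed by a greater-than sign.

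The missing denominator matters most. The limit is meant to flag reactogenicity of the vaccine, but the report that carries it is blinded by default and includes four placebo subjects in every sixteen. A panel member who divides by everyone in the report gets a different figure from one who divides by vaccine recipients, and the two can fall on opposite sides of the limit. These are the only numeric reactogenicity limits in a first-in-human escalation, so each reviewer should be computing the same quantity.

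**Working it through.** **The plan's own figure.** The protocol gives no operating characteristics for these limits. Its only computed probabilities are in section 11.3, for seeing at least one reaction among 12 subjects: 1 − 0.90^12 = 0.718 (stated as about 72%) and 1 − 0.95^12 = 0.460 (stated as about 46%). Both reproduce. They use the 12-subject treatment group as the base.

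**Inputs.** Limits of 70% and 50% (section 9.1.8, Appendix C); 12 vaccine and 4 placebo subjects per cohort (section 5.1.1). Subjects are taken as the counting unit.

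**Counts at which each limit is reached.**

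- Local, by arm: 0.70 × 12 = 8.4, so 9 of 12. Pooled: 0.70 × 16 = 11.2, so 12 of 16. The sign makes no difference.
- Systemic, by arm: 0.50 × 12 = 6, so 6 of 12 (≥) or 7 of 12 (>). Pooled: 0.50 × 16 = 8, so 8 of 16 (≥) or 9 of 16 (>).

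**What pooling does.** Pooled proportion = (V + P)/16, with V vaccine and P placebo reactors.

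- V = 9 (75% by arm, limit reached), with P = 0, 1, 2, 3, 4: 56.25%, 62.5%, 68.75%, 75%, 81.25%. The first three fall below 70%.
- With P = 0, the pooled local limit needs V = 12, that is, every vaccinee.
- V = 6 (50% by arm), P = 0: 6/16 = 37.5%.
- The error can go the other way: V = 8 (66.7%, below the limit) with P = 4 gives 12/16 = 75%.

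**Chance that the limit is reached.** The protocol gives no rates for reactions above grade 2, so the rates here are assumptions. V ~ Bin(12, pv), P ~ Bin(4, pp).

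Local: pooled P(V + P ≥ 12) against by-arm P(V ≥ 9).

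| Vaccine rate | Pooled, placebo 0% | 10% | 25% | 50% | By arm |
|---|---|---|---|---|---|
| 70% | 0.014 | 0.048 | 0.119 | 0.285 | 0.493 |
| 80% | 0.069 | 0.155 | 0.296 | 0.539 | 0.795 |
| 90% | 0.282 | 0.424 | 0.604 | 0.822 | 0.974 |

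Systemic, read as ≥: pooled P(V + P ≥ 8) against by-arm P(V ≥ 6).

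| Vaccine rate | Pooled, placebo 0% | 10% | 25% | By arm |
|---|---|---|---|---|
| 50% | 0.194 | 0.273 | 0.395 | 0.613 |
| 60% | 0.438 | 0.526 | 0.645 | 0.842 |

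Read as >, the by-arm figures are 0.387 and 0.665. The pooled figures are 0.073, 0.126, 0.218 at a 50% vaccine rate and 0.225, 0.311, 0.440 at 60%.

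**Number of reviews.** Two injections in each of cohorts 1 and 2 make 2 × 2 = 4. The review after the first 20 µg dose, named in 5.1.2 and 9.1.8, makes five. Section 5.1.1 stops at four. The total in 9.1.8 is five, but the same sentence attributes all five to cohorts 1 and 2.

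**The case against.** The case for leaving the text alone has four parts.

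- **The limits do not gate escalation.** They are advisory. The working gate is a favourable review of all 7-day data by the Investigator and two advisers. This stands. A reader might infer from the tables that an unsafe dose would probably escalate. The documents do not support that: the probabilities describe whether an advisory figure is reached on one reading of it, and nothing in the protocol says that escalation proceeds while the figures stay below the limits.
- **Pooling is never prescribed.** A reader might infer that the protocol requires a pooled percentage. It does not say whether the report is pooled or by coded arm. Appendix C is a sample that still carries 1 µg and 5 µg dose labels, so its layout is weak evidence. Section 9.1.8 also speaks of harm related to the study vaccine, which favours a vaccine-recipient reading, and reviewers may un-blind. Still, a report that is blinded by default and covers all 16 subjects cannot show the vaccine-arm rate, and un-blinding is discretionary and not tied to the limits.
- **The large gaps need extreme rates.** For redness or swelling, above grade 2 means more than 50 mm (Appendix A). The placebo contains Alhydrogel too, so zero local placebo reactors is the worst case, and the dilution disappears when both arms react alike. At a true vaccine rate of 30%, even the by-arm local limit is reached with probability only 0.002. Reactions above grade 2 also go to the Investigator within 24 to 48 hours. All of this stands and limits the severity.
- **A coded-arm column would un-blind the Investigator.** With 12 against 4, arm sizes reveal allocation, and the Investigator sits on the panel and assigns causality (section 9.1.6). This stands. Permission to un-blind on medical judgement is not permission to disclose arms routinely to everyone.

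**Conclusion.** The point holds as a minor one. The denominator is missing in both places where the limits appear, and the pooled distortion follows from the cohort counts alone: 75% of vaccinees can show as 56% to 69% with 0 to 2 placebo reactors, and 50% as 37.5% with none. That arithmetic assumes only that subjects are counted and that the percentage is taken over all 16. The probabilities also rest on assumed reaction rates.

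The unclear sign matters only for the 50% limit. The review count is a separate contradiction, and it bears on whether the first 20 µg dose gets a 7-day review. The missing cross-reference in 6.7 is a drafting gap between a general rule and a specific exception.

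**What to change.** 1. In 9.1.8 and Appendix C, define each limit as the proportion of vaccine recipients in the cohort with at least one solicited reaction above grade 2 (local and systemic separately) within 7 days of a given dose. State ≥ or >. The counts are then 9/12 local and 6/12 (≥) or 7/12 (>) systemic.
2. Keep the Investigator's report blinded and pooled. Give arm-level counts only to the two independent advisers, either routinely or once the pooled count reaches 9/16 local, or 6/16 (≥) or 7/16 (>) systemic. Because V + P is never below V, this trigger cannot miss a vaccine arm that is at its limit.
3. Name this exception in 6.7.
4. Change 5.1.1 to five reviews. Reword 9.1.8 as one review after each injection in cohorts 1 and 2, plus one after the first 20 µg dose.

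The cost is wording in four places and a separate advisers' table, with some extra un-blinding of the advisers. Under assumed vaccine/placebo rates of 20%/10%, 30%/15% and 40%/20%, all below the limits, the triggers fire with these probabilities:

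| Trigger | 20%/10% | 30%/15% | 40%/20% |
|---|---|---|---|
| Systemic 6/16 | 0.05 | 0.22 | 0.51 |
| Systemic 7/16 | 0.01 | 0.10 | 0.31 |
| Local 9/16 | 0.0005 | 0.01 | 0.06 |

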10.0 DATA COLLECTION AND MANAGEMENT

10.1 Data Collection, CRF Completion

None of the data to be collected during this trial will be estimated, if missing. Once the final study subject has completed the study evaluations and the CRF have been entered and queries resolved, the database can be locked following appropriate QC/Quality Assurance (QA) procedures.

The Investigator must submit a completed CRF for each subject who receives the study vaccine. CRFs should be signed and dated by the Investigator to document his review of the data and acknowledgement that the data are accurate. The CRFs should be completed in blue indelible ink and be legible. If an entry on a CRF requires change, the correction should be made as follows:

Draw a single line through the incorrect entry.

Enter the correct data and initial and date the change. Correction fluids, markers, erasures or any form of obliteration on CRFs are not permitted under any circumstances.

All data fields should be completed. Where a page or pages are unused, the subject’s initials and number must still be entered in the appropriate fields, with a single line drawn through the remainder of the page.

The CRFs should be completed in black pen and be legible. CRF completion guidelines will be issued.

10.2 Data Management

Data management will be performed at PharmaNet Specialized Pharmaceutical Services (SPS).

11.0 STATISTICAL METHODS AND DETERMINATION OF SAMPLE SIZE

11.1 Statistical Methods

Data analysis will be performed at Anapharm Inc.

An interim clinical study report analyzing safety and immunogenicity at 42 days post-vaccination will be completed.

All descriptive and inferential statistical analyses will be performed using SAS^®^ Version 8.2 or higher statistical software. Descriptive statistics for continuous variables will consist of the mean, median, geometric means (where appropriate), standard deviation, minimum, and maximum values. For categorical variables, the number and percent of each category will be displayed. Frequency tables for categorical variables may be performed using Microsoft^®^ Office Excel 2003 or higher version.

For the analysis of safety and immunogenicity endpoints, a two-sided alpha level of 5% will be used. All statistical tests will be two-tailed unless otherwise stated. No attempt will be made to control type I error rate inflation attributable to multiple comparisons.

Demography will be compared among treatment groups using Fisher’s exact test for categorical factors and the Kruskal-Wallis test for continuous factors.

The calculations and statistical analyses will be further described in a statistical analysis plan.

11.1.1 Hypotheses and Statistical Methods for Primary Endpoints

11.1.1.1 Hypotheses

To be defined in the statistical analysis plan.

11.1.2 Statistical Analysis

11.1.2.1 Immunogencity

The geometric Mean Titers (GMTs) with 95% confidence intervals (CI) will be determined at Day 0, Day 21 and Day 42 for each treatment group. Summary statistics of the immunogenicity endpoints (seroconversion factor (GMFR), seroconversion rate and seroprotection rate) will be calculated for each treatment group at each of Day 21 and Day 42.

Seroconversion factor (GMFR) will be compared between treatment groups using ANOVA at each of Day 21 and Day 42. Statistical analyses will be performed on log-transformed data. If a statistically significant treatment effect is found, multiple comparisons will be done using Duncan’s multiple range test.

Seroconversion rates and seroprotection rates will be compared (each vaccine dose level versus placebo) using Fisher’s exact tests at each of Day 21 and Day 42.

11.1.2.2 Safety

Safety endpoints will be compared (each vaccine dose level versus placebo) using Fisher’s exact tests.

11.1.3 Hypotheses and Statistical Methods for Exploratory Endpoints

(Refer to Statistical Analysis Plan)

11.2 Population to be Analyzed

11.2.1 Definition of Population

11.2.1.1 Intent-to-Treat Safety Analysis Set

The Safety Set is defined as all subjects who received any study treatment.

11.2.1.2 Full Analysis (Intent-to-Treat) Immunogenicity Population

The Full Analysis Set will consist of the subset of the Safety Set with a Day 0 and any post-vaccine immunogenicity assessment. Subjects who received the wrong treatment will be analyzed as randomized.

11.2.1.3 Per-Protocol Immunogenicity Population

The Per Protocol Set will consist of the subset of the Full Analysis Set who completed the study with no major protocol violation. For the Day 21 analysis, this should include the subjects who received the first vaccine dose and had Day 0 and Day 21 immunogenicity measurements. For the Day 42 analysis this should include the subjects who received both vaccine doses and had Day 0 and Day 42 immunogenicity measurements.

11.2.2 Populations Used in Analysis

Safety analyses will be carried out on the Safety Set. Primary immunogenicity analyses will be performed on the Per Protocol Set. If necessary, the Full Analysis Set could also be used for immunogenicity analyses.

11.3 Determination of Sample Size and Power Calculation

The sample size is limited as this is a first-in-human study. Nevertheless, 12 subjects per treatment groups will allow observing an adverse reaction having 10% incidence with about 72% probability. An adverse reaction having 5% incidence will be observed with about 46% probability.

12.0 ETHICAL AND LEGAL ISSUES AND INVESTIGATOR / SPONSOR RESPONSIBILITIES

12.1 Ethical Conduct of the Trial / Good Clinical Practice

The study will be conducted in accordance with the ethical principles that have their origins in the most recent update of the Declaration of Helsinki, International Conference on Harmonization (ICH) Guideline E6, GCP rules and applicable Canadian regulatory requirements.

The Investigator is responsible for obtaining written approval for the clinical study protocol (including all protocol amendments), the written subject informed consent form, informed consent updates, subject recruitment procedures (e.g. advertisements) and any other written information to be provided to the subject which complies with local regulatory requirements.

The Investigator is responsible for maintaining a copy of the approval document in the study documentation files and for providing a copy to Medicago R&D Inc.

The Investigator should submit written reports of the clinical study status to the IEC/IRB annually or more frequently if requested by the IEC/IRB. A final study notification should be forwarded to the Independent Research Ethics Committee within 90 days after the study has been completed or in the event of premature termination of the study. Copies of all clinical study status reports (including termination) should be provided to Medicago R&D Inc. The end of the trial is defined as the date of the last contact with any participant in the trial. The end of the trial must be notified to the IEC/IRB and Health Canada within 90 days or within 15 days if the trial is halted or terminated early.

Following the reporting of serious adverse reactions and events to Medicago R&D Inc. (Section 9.1.1) the Investigator must also promptly inform the IEC/IRB of these; or other safety related information reported from Medicago R&D Inc.

Modifications to the protocol should be made as an amendment and should be approved/acknowledged both by Medicago R&D Inc. and the IEC/IRB prior to being implemented unless the amendment is made to eliminate an immediate hazard to the clinical study subjects. Medicago R&D Inc. shall be responsible for notifying the appropriate regulatory authorities of any substantial amendments to the protocol.

The Investigator is responsible for notifying the Independent Research Ethics Committee of all protocol amendments.

Administrative amendments (e.g. changes in telephone number, etc.) will not require approval by the Independent Research Ethics Committee unless requested by the IEC/IRB.

